**Supplementary Figure S1: Flow diagram summarizing the process of the trial**

Identify patient with post-stroke depression

Check eligibility

Consent

**Collect baseline data**: physical exam, vital signs, computerized cognitive tests, questionnaires, psychiatric assessment, blood samples.

Start treatment with 300 mg/day Maraviroc

**Follow-up assessment on week 2 and weeks 4, 7, and 10:** physical exam, vital signs, computerized cognitive tests (at week 10), questionnaires, psychiatric assessment, record of AEs related or not related to the medication assignment, concomitant medications, pill counts, blood samples.

**Telephone contact assessment on weeks 3, 5, 8, and 9:** record of AEs, and concomitant medications.

**Follow-up assessment on weeks 14, and 18 (post-treatment assessments):** physical exam, vital signs, questionnaires, psychiatric assessment.

Supplemental Methods: Sample size calculation

The percentage of pilot study participants who tolerate a new treatment or the proportion of eligible patients who provide informed consent for participation would be representative of the tolerance or participation rates if all potential participants were studied. Providing a means to estimate these quantities enables early indicators of treatment tolerability and enrollment feasibility.

Weight gain and sexual dysfunction are well documented with the current anti-depressants, usually selective serotonin reuptake inhibitors (SSRIs) or Serotonin-Norepinephrine Reuptake Inhibitors (SNRIs). Another side effect of SSRIs is hyponatremia, which can limit their use in stroke patients.

It is of clinical interest to identify augmentative therapies that can alleviate some of the known side effects affecting a high percentage of patients receiving SSRIs or SNRIs (an average of 30% of people treated with an SSRI reported sexual dysfunction^1^, while 25% of individuals had a significant body weight increase^2^ and an average of 22% had hyponatremia^3^). Therefore, it is desirable to rule out potential treatments not consistent with this rate of sexual dysfunction, weight gain, and hyponatremia before considering more conclusive testing. Using the following equation,

**
[figure not shown]
**

(where π is the probability of the adverse event of interest)

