**Based on Pfizer’s reports on premarketing and post marketing studies of Maraviroc and review of the literature, no dose adjustment is necessary even in patients with mild-to-moderate renal impairment. The drug does not affect the QT interval.** **At high doses (600 mg or more), it may induce orthostatic hypotension, so it is recommended that users who also take antihypertensive medications be asked about symptoms of orthostatic hypotension.** Of note, 8% of patients in active and placebo drug groups described orthostatic symptoms in a large trial. In HIV trials, 1.3% of subjects had cardiovascular events, more than in the placebo group, but the link to the drug was unclear and symptoms occurred only in those with known cardiac disease. Also, no greater incidence of infection, rash or other CNS symptoms were noted in these patients. **An occasional Stevens-Johnson syndrome and drug rash with eosinophilia and systemic symptoms did occur (seen only in postmarketing surveillance, not in controlled trials), so complaints of rash, fever, joint or muscle aches, blisters, facial edema etc. will be part of our weekly phone call surveillance plan. Participants will be told to stop their medication immediately should such symptoms occur, and their physician will be notified.** Of note, St John’s wort should not be used with Maraviroc, since it decreases the concentration of the medication.

**Maraviroc is metabolized by the liver, so using it in persons with more than mild hepatic disease, especially in the presence of a CYP3A inhibitor, would have to be closely monitored; we will therefore not include these patients in this study.**

Clinical aspects

**Pharmacokinetics**: Maraviroc pharmacokinetics was studied in 28 phase I/IIa studies (complete profiles) and 3 phase IIb/III studies (with sparse sampling). The evaluation was performed after single-dose intravenous administration (1–30 mg) as well as oral single-dose (1–1200 mg) and multiple-dose administration (3–900 mg twice daily [BID] and 1200 mg once daily [QD]). The following formulations were used during development: powder for oral solution in phase I, 5 mg/25 mg/50 mg/100 mg/150 mg tablets in phase I/IIa and 150 mg in phase IIb/III. An intravenous formulation was used to determine absolute bioavailability. The commercial formulations (150 mg, 300 mg) were not used in the clinical trials. The analytical methods used to analyze Maraviroc have been adequately validated.

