**Recruitment and retention plans**

Screening and patient evaluation:

Participants will be out-patients referred from the community or the hospital’s ambulatory services, who meet entrance and exclusion criteria. After receiving a detailed explanation and signing informed consent, the participant will be further screened. All identifying information of participants will be saved in a separate password protected study log available only to study investigators. All the gathered data will be de-identified and coded with a pre-assigned study ID.

Eligible patients enrolled in the study will undergo a baseline visit (Week 1), in which they will receive the study drug following completion of all relevant assessments. During the first administration, participants will remain under clinical supervision and vital signs monitoring for 2 h at the Tel Aviv Sourasky Medical Center. Blood pressure and heart rate will be recorded before discharge. Patients will be evaluated every 2 weeks during the trial using multiple depressive, anxiety and functional questionnaires as well as cognitive tests. A final safety and efficacy assessment will be held 8 weeks after the patient’s last dose (Week 18).

Open-label treatment period:

On Day 1, subjects will start the study drug. A 1-week supply of capsules will be handed to participants after the consent has been signed, and baseline measurements obtained, usually on the same day. The second 2-weeks supply will be provided during a scheduled interim measurement assessment at TLVMC near the end of the 2nd week on medication. Participants will take Maraviroc 300 mg at 6-8AM. The capsules will be supplied by the hospital pharmacies and used under IRB approval as required.

The efficacy, safety, and biomarker evaluations that will be performed at each visit of the treatment phase and are described in the Time and Event Schedule.

Post-treatment phase

The efficacy and safety evaluations that will be performed at each visit during the post-treatment phase are described in the Time and Event Schedule.

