All subjects who receive at least 1 dose of study medication should have 2 follow up visits conducted at 4 and 8 weeks after the last dose of study medication. The follow up visits at weeks 3, 5, 8, 9 will be telephone contacts. The follow up visit at 4 and 8 weeks after the last dose of study medication are clinic visits. Any clinically significant abnormalities persisting at the end of the study will be followed by the investigator until resolution or until a clinically stable endpoint is reached. All adverse events and special reporting situations, whether serious or non-serious, will be reported until completion of the subject's last study-related procedure (which may include contact for follow-up of safety).

TIME AND EVENTS SCHEDULE (Table S1)

| **Week 14 (4 weeks after last dose, Week 18 (8 weeks after last dose)** | **Telephone contact (week 3, 5, 8, 9)** | **week 4, week 7, week 10** | **Week 2** | **Day 1 (can be the same as screening)** | **Screening** | **Participant Assessment** |
| --- | --- | --- | --- | --- | --- | --- |
|  |  |  |  |  | **X** | Informed consent |
|  |  |  |  |  | **X** | Inclusion / Exclusion criteria |
|  |  |  |  |  | **X** | Medical history, demographics |
|  |  | **X** | **X** | **X** |  | Study Drug Administration |
|  |  |  |  |  |  | Safety Assessments |
| **X** |  | **X** | **X** | **X** | **X** | Physical examination |
|  |  | **X** | **X** | **X** | **X** | Body weight |
|  |  | **X** | **X** | **X** | **X** | Vital signs |
|  |  | **X** | **X** | **X** | **X** | 12-lead ECG |
|  |  |  |  |  | **X** | Carotid Doppler |
|  |  |  |  |  |  | Clinical Laboratory assessments |
|  |  | **X** | **X** |  | **X** | Hematology, Chemistry |
|  |  | **X** | **X** |  | **X** | Serum cytokines |
|  |  |  |  |  |  | Efficacy assessments |
| **X** |  | **X** | **X** | **X** | **X** | MADRS (7-day recall) |
| **X** |  |  |  | **X** |  | GDS |
|  |  | **X** | **X** | **X** | **X** | CGI-I + CGI-S |
| **X** |  | **X** | **X** | **X** | **X** | QIDS-SR16 |
|  |  | **X** | **X** | **X** | **X** | PGI-S |
| **X** |  | **X** | **X** | **X** | **X** | PGI-C |
| **X**  (for suspected Dementia) |  |  |  |  | **X** | GAD-7 (7-day recall) |
| **X** |  | **X (week 10)** |  |  | **X** | MoCA |
| **X** |  | **X (week 10)** |  | **X** |  | Computerized cognitive test battery (Neurotrax) |
| **X** |  |  |  | **X** |  | SIS |
| **X** |  | **X** |  | **X** |  | ADL |
| **X** |  |  |  | **X** |  | RNL |

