|  |  |  |  |  |  | Ongoing Subject Review |
| **X** | **X** | **X** | **X** | **X** |  | Concomitant therapy^2^ |
| **X** | **X** | **X** | **X** | **X** |  | Adverse events^3^ |

^1^Visit window: Day 15 (+/- 1 day), Day 29, 43, 57 and 71 can occur +/- 3 days.

^2^Concomitant therapies must be recorded throughout the study beginning with signing of the informed consent until the last follow up visit.

^3^All adverse events and special reporting situations, whether serious or non-serious, will be reported from the time a signed and dated informed consent form is obtained until completion of the subject's last study-related procedure (which may include contact for follow-up of safety.

Abbreviations: **ADL** = the activities of daily living; **CGI-I =** clinical global impression – improvement; **CGI-S** = Clinical Global Impression – Severity (S); **ECG** = electrocardiogram; **GAD-7** = Generalized Anxiety Disorder 7-item scale; **GDS =** Geriatric depression scale; **MADRS** = Montgomery Asberg Depression Rating Scale; **MoCA** = Montreal Cognitive Assessment**; PGI-C** = Patient Global Impression of Change; **PGI-S** = Patient Global Impression – Severity; **RNL** = Reintegration to Normal Living Index; **SIS** = stroke impact scale (SIS).

**QIDS-SR16** = 16-item Quick Inventory of Depressive Symptoms- Self Report.

Laboratory work up: Blood samples for: cell blood count, lipids profile, liver and kidney function, inflammatory markers: highly sensitive c-reactive protein (hs-CRP), tumor necrosis factor (TNF)-alpha, interleukin-6 (IL-6), IL-10, IL-1 β, IL-2, IL-17A. Cytokine level will be determined using ELISA (R&D Systems, USA) and ProcartaPlex™ Multiplex Immunoassay (Affymtrix eBioscience) at the research laboratory for Stroke and dementia, Tel Aviv Sourasky Medical Center.

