**Interventions:**

Our participants will be free of hepatic, as well as renal impairment. The recommendation from the FDA is to obtain liver function tests prior to starting the drug and again should symptoms such as rash or hepatitis occur. This rather rare adverse reaction tends to occur at about one month after starting the medication (in less than 4% on the drug or placebo), so the investigators will obtain a bilirubin and transaminases at the planned 1-month follow up.

Adverse events related to the medication assignment, to rehabilitation practice or to other causes will be adjudicated by the safety committee with input from the principal investigator.

Patients will be contacted weekly by phone to help maintain interest in the trial, assure use of the assigned medication, and ask about possible adverse reactions. The coordinator will obtain this information and provide the feedback using a standard script and checklist.

**Quality control and analysis:**  All patient records and specimens will be tracked in a manner consistent with Good Clinical Practice by a quality-controlled, auditable, and appropriately validated laboratory information management system, to ensure compliance with data confidentiality as well as adherence to authorized use of specimens as specified in this protocol and in the Informed Consent Form.

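### The protocol commits to weekly phone contact for safety, but its schedule leaves two 14-day intervals without contact, and its visit days and post-treatment vital signs do not agree

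*Protocol*

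**What the plan says.** **Phone contact.** The Toxicology section notes severe skin and hypersensitivity reactions seen after marketing, and says that asking about their symptoms "will be part of our weekly phone call surveillance plan". The Interventions section that precedes the quality control paragraph says "Patients will be contacted weekly by phone to help maintain interest in the trial". It gives adherence and adverse reactions as further purposes, and has the coordinator work "using a standard script and checklist".

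The schedule differs. Figure S1 has "Telephone contact assessment on weeks 3, 5, 8, and 9". The Post-treatment phase text says "The follow up visits at weeks 3, 5, 8, 9 will be telephone contacts", and the Table S1 column heading gives the same four weeks.

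**Clinic days.** Table S1, Figure S1 and the follow-up assessment paragraph after the table put on-treatment visits at weeks 2, 4, 7 and 10. Footnote 1 to Table S1 gives Day 15 with a one-day window and then "Day 29, 43, 57 and 71 can occur +/- 3 days". The screening and evaluation text under Recruitment and retention plans says "Patients will be evaluated every 2 weeks during the trial".

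**Vital signs at weeks 14 and 18.** Figure S1 lists them, as does the follow-up assessment paragraph. In Table S1 the physical examination row is marked for these two visits and the vital signs row is blank. The Post-treatment phase text refers to that schedule for what is done at each visit.

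**The concern.** Safety and tolerability are the primary objective. The weekly call is the safeguard that the protocol names for detecting a serious skin reaction early, and the visit schedule does not deliver it. Staff who work from Table S1 would not question a patient between the supervised first dose and about Day 15, and would leave a second two-week interval later in treatment.

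The conflict in clinic days adds to this. It is unclear whether there are four or five on-treatment visits after Day 1, and Day 57 is a clinic day in the footnote but a phone call in the table heading. These visits carry the ECG, laboratory tests and MADRS.

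Heart rate and blood pressure are a named secondary safety objective. Readings after withdrawal would show whether a change on drug reverses, and Table S1 does not ask for them.

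**Working it through.** **Inputs**
- Clinic weeks 2, 4, 7, 10 (Table S1, Figure S1, follow-up assessment paragraph).
- Call weeks 3, 5, 8, 9 (Figure S1, Post-treatment phase text, Table S1).
- Footnote days 15, 29, 43, 57, 71 (Table S1, footnote 1).
- Assumption: the weekly commitment covers the 10 treatment weeks, since one purpose of the calls is to check use of the drug.

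**Numbering.** Taking week k as Day 7k + 1, week 2 is Day 15 and week 10 is Day 71. This matches the footnote, and also Table S1, where week 14 is 4 weeks after the last dose and week 18 is 8 weeks after.

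**Calls alone.** Four calls are scheduled, against about 10 if a phone call is meant every week.

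**Counting clinic visits as contacts.** Weeks without a clinic visit are 1, 3, 5, 6, 8 and 9. Removing the call weeks 3, 5, 8 and 9 leaves weeks 1 and 6. In days:

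| Schedule | Contact days | Gaps (days) |
|---|---|---|
| Table S1 | 1, 15, 22, 29, 36, 50, 57, 64, 71 | 14, 7, 7, 7, 14, 7, 7, 7 |
| Footnote days replace week 7 | 1, 15, 22, 29, 36, 43, 57, 64, 71 | 14, 7, 7, 7, 7, 14, 7, 7 |
| Weekly commitment met | 1, 8, 15, 22, 29, 36, 43, 50, 57, 64, 71 | all 7 |

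Both scheduled versions contain two 14-day gaps. The one-day window on Day 15 makes the first gap 13 to 15 days (14 − 1 to 16 − 1).

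**Does the answer depend on the numbering?** The screening and evaluation text calls the Day 1 visit Week 1. If that label is accepted, only week 6 is an empty week, but the interval from Day 1 to about Day 15 is still 14 days. The second gap, from week 5 to week 7, is 14 days under any numbering.

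**Clinic days.** The footnote days convert by (day − 1)/7 to weeks 2, 4, 6, 8 and 10. Weeks 6 and 8 are not clinic weeks in Table S1, and week 7 has no footnote day. Week 7 is Day 50, and 50 − 43 = 57 − 50 = 7 days. The 3-day window cannot reconcile them.

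**Vital signs.** Table S1 leaves them blank at 2 of 2 post-treatment visits. Screening, Day 1 and on-treatment readings are all marked, so the change from baseline planned under Statistical Analysis can still be produced on treatment.

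**The case against.** Several arguments on the other side have force.

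- **The Day 1 visit is itself a Week 1 contact.** It includes full assessments, a supervised first dose and two hours of monitoring. This stands as to the label, so it is wrong to say that week 1 has no contact. The accurate statement is a 14-day interval after Day 1.
- **The texts can coexist.** Nowhere does the protocol restrict calls to weeks 3, 5, 8 and 9, so weekly calling would not breach Table S1. That is correct, and no omitted call is shown. But three places list the same four weeks and none points to further calls, so the schedule does not carry the commitment.
- **Collection of events is continuous.** Adverse events are reported from consent to the last study procedure, volunteered events count, and patients are told to stop the drug at once if such symptoms occur. The Interventions section places the expected rash or hepatitis reaction at about one month, when contact is weekly (weeks 2 to 5). This stands, and it limits the harm to later detection and longer recall.
- **One site, one coordinator role.** A reader might infer that different sites would follow different texts. The trial has a single center and 10 patients, so that does not apply.
- **The blank vital signs cells may be a layout slip.** Table S1 has at least one other apparent misplacement: a note on suspected dementia in the GAD-7 row. The follow-up assessment paragraph is also weak evidence, because its pooled list puts pill counts at visits when patients are off drug. Figure S1, however, lists vital signs for weeks 14 and 18 specifically, so the conflict remains. What the documents show is disagreement, and they do not show that the readings are lost.

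**Conclusion.** The inconsistencies are in the current text and are worth correcting, but their weight is modest. Counting every scheduled contact, there are two 14-day intervals in the treatment phase where the text commits to 7-day contact. The position of the second depends on which clinic days govern, but neither reading removes it. This rests on week k being Day 7k + 1 and on the weekly commitment covering the treatment phase.

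What is exposed is early detection and recall of non-serious events, and possibly blood pressure and heart rate after withdrawal. A reader might infer that serious events would be missed or that the primary safety endpoint is undermined. The documents do not support that. The endpoint concerns serious events and events leading to discontinuation, reporting is continuous, and capturing serious events does not depend on a call at Day 8. Nor is on-treatment change from baseline in vital signs affected. No sample size or error rate is involved.

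**What to change.** 1. **Calls.** Add a scripted call at about Day 8 and one in the remaining empty week (about Day 43 if week 7 is kept, about Day 50 if the footnote days are kept) to Table S1, Figure S1 and the Post-treatment phase text. Reword Toxicology and Interventions as weekly contact by phone or clinic visit. Every gap is then 7 days.
2. **Clinic days.** Choose one schedule and make footnote 1, the statement of two-weekly evaluation, Table S1, Figure S1 and the follow-up assessment paragraph agree. Days 15, 29, 50 and 71 need the fewest edits, because Table S1, Figure S1 and that paragraph already use weeks 2, 4, 7 and 10. The footnote days are equally valid, but they mean five on-treatment visits after Day 1 where Table S1 has four, and the week 8 call becomes a visit.
3. **Vital signs.** Mark them at weeks 14 and 18 in Table S1.

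**Cost.** Two calls for each of 10 patients, so about 20 short calls by the existing coordinator. Vital signs at two visits for 10 patients, so 20 sets of readings at visits that already include a physical examination. The footnote-day option would add one clinic visit per patient, 10 in all. The rest is wording, and eligibility and sample size do not change.

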# A large, open-label safety study of Maraviroc was conducted at 262 sites worldwide in 1032 R5 HIV-positive, treatment-experienced patients. The data demonstrated that Maraviroc was well tolerated alone and in combination with other antiretroviral medications.^33^ Despite concerns regarding the hepatic safety of CCR5 antagonists, an extensive data analysis did not show a significant difference in severe hepatotoxic effects between Maraviroc and placebo.^34,35^

Design:

# We plan to perform a proof-of-concept open label add-on clinical trial of 300 mg Maraviroc given once daily for 10 weeks in 10 patients with PSD. Depression scores over time will serve as outcome measures and each patient function will be compared before and after treatment with study drug, beyond current treatment with other anti-depressants, such that the efficacy will be analyzed only beyond the efficacy of current treatments. The study will consist of 3 phases: (1) screening, (2) open-label treatment (weeks 1-10), and (3) post-treatment follow-up (8 weeks). The primary objective will be safety and tolerability of Maraviroc 300 mg per day in subjects with PSD. If proved safe, we plan continued research to establish efficacy using different dosages of Maraviroc

Objectives

# This study will evaluate the safety and efficacy of Maraviroc 300 mg per day in patients suffering from PSD.

Primary objective:

1. To investigate the safety and tolerability of Maraviroc 300 mg per day in subjects with PSD.

Secondary Objectives:

1. To investigate the safety and tolerability of Maraviroc 300 mg in PSD subjects, with special attention to: effects on heart rate and blood pressure.
2. To evaluate the efficacy of Maraviroc 300 mg per day in improving depressive symptoms in subjects with PSD, as assessed by a change from baseline in the Montgomery-Asberg Depression Rating Scale (MADRS) total score and in improving cognitive, functional, and behavioral outcomes.

To evaluate the effect of treatment with Maraviroc 300 mg per day for 10 weeks on blood inflammatory markers in subjects with PSD.

3. To assess the effect of Maraviroc 300 mg in PSD subjects on: a. Depressive symptoms, as assessed by the 16-item Quick Inventory of Depressive Symptomatology- Self Report (QIDS-SR16) b. Remission, defined as a MADRS total score ≤10 c. Response, defined as a ≥50% reduction from baseline in MADRS total score d. The severity of illness using the Clinical Global Impression - Severity (CGI-S) and the Patient Global Impression - Severity (PGI-S) e. Symptoms of anxiety as assessed by the Generalized Anxiety Disorder 7-item Scale (GAD-7). d. Cognitive status, as assessed by cognitive score based on repeatable computerized battery of cognitive tests (Neurotrax) and Montreal Cognitive Assessment (MoCA). e. Functional outcome, as assessed by the stroke impact scale (SIS), the activities of daily living (ADL) score, and Reintegration to Normal Living Index (RNL).

Methods

We plan to enroll ten adults with PSD.

